### 2.8. Statistical Analysis

The baseline measures will be compared with the measures obtained under interventions A and B. The normality of data will be tested by the Shapiro–Wilk test. Repeated-measures ANOVA with the Bonferroni correction for multiple testing, followed by Tukey’s honestly significant difference tests will be used as the parametric test for normally distributed data. If the data do not follow a normal distribution, a non-parametric test, the Kruskal–Wallis test with the Bonferroni correction for multiple testing followed by Dunn–Bonferroni tests, will be used. The data will be presented as either the mean ± standard deviation or median (interquartile range) for normal and non-normal distributions. All statistical analyses will be performed using SPSS software (version 25, IBM Japan, Tokyo, Japan). All *p* values are two-tailed and a *p* value of <0.05 is considered to indicate statistical significance.

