### 2.5. Sample Size and Allocation Concealment Mechanism

In a previous study that evaluated the effect of tongue protrusion using a tongue-stabilizing device on the severity of OSA, Apnea Hypopnea Index (AHI) improved from 21.8 ± 8.6/h to 9.3 ± 5.8/h [18]. This indicates that, if intervention B is applied to a participant, there should be no change in AHI. Therefore, our null hypothesis is that the mean AHI was not different between intervention A (μ1) and intervention B (μ2) (i.e., μ1 = μ2), whereas the alternative hypothesis is that the mean AHI of intervention B is greater than that of intervention A (i.e., μ1 < μ2). The effect size (Δ0) and the power (i.e., 1-β) should be calculated with the following formula: Δ0 = (μ1 − μ2)/σ, 1 − β = Pr{t0 < −t(φ, 2α)}, φ = n1 + n2 − 2, where σ is the population standard deviation, β is the Type II error, φ is the degree of freedom, α is the Type I error set at 0.05, n1 is the number of subjects with intervention A, and n2 is the number of subjects with intervention B. Statistically, n1 and n2 are assumed to be equal (i.e., n1 = n2) to each other and 1-β is set at 0.80. Consequently, each intervention group needs 9 participants (i.e., 18 participants for both groups). If the drop-out rate is set rather high, at 30%, the study needs 25.7 samples; thus, a total of 26 participants will be required to test the hypothesis.

These 26 participants are to be randomized by creating a computer-generated randomization list using the permuted block method (Mujinwari, https://mujinwari.biz, Iruka-system, Tokyo, Japan: accessed on 28 May 2023) with random block sizes of two or four, stratified by body mass index (<25 kg/m^2^ or 25 kg/m^2^≤). Consequently, participants will be assigned random numbers based on consecutive enrollment into either sequence AB or sequence BA, which provides an approximately one-to-one ratio for the number of subjects in the two sequences.

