The predetermined random allocation order will be strictly applied to all consecutive consenting patients during the study period. The anesthesiologist ([name]) will be informed of the allocation of the participant immediately before the initiation of intravenous sedation to reduce potential bias. The anesthesiologist will provide conscious intravenous sedation by a bolus intravenous injection of midazolam (1 to 3 mg) and propofol (5 to 10 mg), followed by continuous infusions of propofol (1 to 3 mg kg^−1^ h^−1^) using the target-controlled infusion system [19,20]. After an acclimatization period for TPR (30 s), a baseline evaluation (i.e., no control of tongue position with TPR in place) will be performed (1 min) (Figure 4). Thereafter, each patient will undergo both interventions A (MAX50 for 1 min and MAX 100 for 1 min) and B (1 min) in a randomized order with a washout period (30 s) between the interventions. An ex-post evaluation (1 min) will also be scheduled after removal of the TPR, when both study sequences are complete. After the core part of the present study (i.e., baseline evaluation, interventions, and ex-post evaluation) which will take an average of 6 min, supplemental oxygen at a flow rate of 3 L/min will be provided for the scheduled dental operation.

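### Section 2.8 leads with contrasts against a baseline minute that always comes first, does not name the A-versus-B contrast that sizes the trial as primary, and has no period term

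*Protocol article*

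**What the plan says.** Section 2.1 of the protocol article declares a randomised two-sequence (AB/BA) crossover. Section 2.5 states the hypothesis for the sample size: "our null hypothesis is that the mean AHI was not different between intervention A (μ1) and intervention B (μ2"); the alternative is that "the alternative hypothesis is that the mean AHI of intervention B is greater than that of intervention A".

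Section 2.6 fixes the order of events. After 30 s of acclimatisation to the tongue position retainer (TPR) there is one baseline minute with the TPR in place but no control of tongue position. Then come A (two minutes, one at MAX 50 and one at MAX 100) and B (one minute) in randomised order, separated by a 30 s washout. At the end, "An ex-post evaluation (1 min) will also be scheduled after removal of the TPR".

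Section 2.8 begins: "The baseline measures will be compared with the measures obtained under interventions A and B". It then names repeated-measures ANOVA followed by Tukey's test, or Kruskal–Wallis followed by Dunn–Bonferroni tests if the data are not normal. It mentions neither period nor sequence and does not use the ex-post minute. The Introduction makes two claims objectives: that A and B each improve on no control, and that A is better than B.

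**The concern.** Randomising the order of A and B protects one comparison, A versus B. It does not protect A or B against baseline, because baseline is never anywhere but first. Sedation starts with bolus doses and continues by infusion. If its depth changes over the six minutes, the change is inseparable from the device effect in both baseline contrasts. Lightening would look like benefit; deepening would hide benefit.

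The contrast with randomised support is the one Section 2.5 powers, yet Section 2.8 gives it no special standing and analyses it without the period term that an AB/BA design calls for. Followed as written, the section puts its leading comparison where randomisation gives no protection.

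**Working it through.** **The plan's own figures.** Section 2.5 takes a difference of 21.8 − 9.3 = 12.5/h. With SD 8.6, d = 12.5/8.6 = 1.453, and a two-sided 5% two-sample t-test reaches 80% power at 9 per group (power 0.825). 18/0.7 = 25.7, hence 26. So the stated size reproduces, and it is a size for A versus B. The Section 2.6 timeline also reproduces: 0.5 + 1 + (2 + 0.5 + 1) + 1 = 6.0 min, the duration given there.

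**Window midpoints** (minutes from the start of acclimatisation, A scored over both its minutes):

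| Window | Sequence AB | Sequence BA | Mean at 1:1 |
|---|---|---|---|
| Baseline | 1.0 | 1.0 | 1.0 |
| A | 2.5 | 4.0 | 3.25 |
| B | 4.5 | 2.0 | 3.25 |
| Ex-post | 5.5 | 5.5 | 5.5 |

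**Bias from a linear drift of g events/h per minute.**
- A minus baseline and B minus baseline: (3.25 − 1.0)g = 2.25g each. For scale, a fall of 12.5/2.25 = 5.6/h per minute would by itself produce the planning difference.
- A minus B: −2g in sequence AB and +2g in BA, so 0 at 1:1.
- A minus B at a 7:11 split (7 AB, 11 BA) without a period term: (11×2 − 7×2)g/18 = 8g/18 = 0.44g.
- A minus B with a period term: (−2g + 2g)/2 = 0 at any split.

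**Precision of A minus B.** Without a period term the ±2g between sequences enters the error: SD = √(SD² + (2g)²).

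**Illustration by simulation** (20,000 runs). Assumed: within-patient SD 5/h per measurement and linear drift; 18 completers split 9:9 unless stated. False-positive rates are with no device effect; power is for a true A–B difference of 5/h.

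| Drift g (/h per min) | 0 | 1 | 2 | 4 |
|---|---|---|---|---|
| False positives, A vs baseline, Tukey | 0.02 | 0.14 | 0.52 | 0.98 |
| Same, n = 26 | 0.02 | 0.21 | 0.73 | >0.99 |
| Type I error, A vs B, paired, no period term | 0.05 | 0.04 | 0.03 | 0.003 |
| Power, A vs B, Tukey | 0.71 | 0.69 | 0.64 | 0.44 |
| Power, A vs B, paired, no period term | 0.81 | 0.79 | 0.71 | 0.43 |
| Power, A vs B, period-adjusted | 0.80 | 0.81 | 0.81 | 0.81 |

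**How far this depends on the SD.** The windows last one or two minutes, so one apnea counts as 60/h or 30/h. Assume Poisson counts at the Section 2.5 rates (21.8/h in one minute, 9.3/h in two). The SD of a difference is then √(60×21.8 + 30×9.3) = √1587 = 39.8/h. Drift of 5.6/h per minute raises it only to 41.4/h, about 4%. The standard error at 18 completers is 39.8/√18 = 9.4/h. The baseline-contrast bias at g = 2 and g = 4 is 4.5/h and 9.0/h, about 0.5 and 1.0 standard errors. Under this assumption the rates in the table overstate the effect, but the bias of 2.25g is unchanged and does not shrink with more participants.

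**How far it depends on scoring A.** If only the MAX 50 minute counts, A averages (2.0 + 3.5)/2 = 2.75 min in the order listed in Section 2.6, or (3.0 + 4.5)/2 = 3.75 min in the order implied by Section 2.4. A minus baseline then carries 1.75g or 2.75g. A minus B carries −0.5g or +0.5g even with balanced sequences, and a period term does not remove it.

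**The case against.** The strongest reply is that sedation is actively controlled: Section 2.6 describes target-controlled infusion with electroencephalogram monitoring, and the Discussion says depth can be held at a chosen level throughout. If so, drift may be negligible. That is fair, and nothing in the documents shows that drift occurs. But it is an assertion that Section 2.8 does not check. It is also fair that an article leaves model detail to a fuller document. The point here is narrower: the comparison and tests that Section 2.8 does fix do not match the design in 2.1 or the hypothesis in 2.5.

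Several stronger readings are not supported:
- A reader might infer that A versus B is never tested. Tukey and Dunn–Bonferroni are all-pairs procedures, so it is tested; it is not singled out or adjusted for period.
- A reader might infer that drift biases A versus B or produces false positives there. With balanced sequences and A scored over both minutes, linear drift does neither; the unadjusted test becomes conservative.
- A reader might fault the missing BMI stratum used in randomisation. A BMI main effect cancels within participants, so its omission matters little.
- A reader might object to comparing with no control at all. That is a stated objective; the difficulty is the fixed order.
- A reader might propose the mean of baseline and ex-post as the reference, since (1.0 + 5.5)/2 = 3.25 min cancels linear drift. But Section 2.6 defines no control with the TPR in place, and the ex-post minute follows its removal. The average would blend two conditions.

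**Conclusion.** The point stands in limited form. Section 2.8 leads with two non-randomised contrasts, each carrying 2.25 min of any linear drift under sedation. It neither names A versus B as primary nor adjusts it for period. For A versus B the consequence is lost precision when sequences are balanced, and a bias of about 0.44 times the drift per minute at an illustrative 7:11 split after dropout.

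The timing figures follow from Section 2.6, given linear drift and A scored over both minutes. The size and direction of drift, the SD of 5/h, the Poisson counts and the 7:11 split are assumptions. The practical effect could be large if drift is marked and measurements are precise, or modest if counting noise in such short windows dominates.

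**What to change.** In Section 2.8:
1. Name A versus B as the primary contrast, in line with Section 2.5.
2. Estimate it with a within-participant crossover model containing treatment and period. Sequence may be added; BMI stratum is optional and will change little.
3. State which minutes of A are scored, because the cancellation of drift depends on it.
4. Keep the baseline with the TPR in place as the no-control reference, and label A and B versus baseline as non-randomised comparisons that may reflect time under sedation.
5. Use the ex-post minute only as a drift check or sensitivity analysis, noting that a baseline-to-ex-post difference mixes drift with removal of the TPR.
6. Carry the same structure into the non-parametric fallback, for example a rank-sum comparison of period differences between the two sequences. That Kruskal–Wallis ignores the pairing is a related but separate matter.

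No new data are needed. The cost is one degree of freedom for period (with 18 completers, 17 falls to 16) and more cautious wording of the claims against no control.

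### Section 2.8 tests A versus B with Tukey's HSD on a pooled three-condition error plus a Bonferroni correction of undefined family, so the sized contrast is judged far more strictly than the 5% used for sizing

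*Protocol article*

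**What the plan says.** Section 2.5 gives one null hypothesis: "our null hypothesis is that the mean AHI was not different between intervention A (μ1) and intervention B (μ2"). The alternative is directional: "the alternative hypothesis is that the mean AHI of intervention B is greater than that of intervention A". The sizing is a two-group t-test in which "α is the Type I error set at 0.05" and "1-β is set at 0.80", with no allowance for multiple comparisons. Its planning figures come from a study of a tongue-stabilizing device: "AHI) improved from 21.8 ± 8.6/h to 9.3 ± 5.8/h". B is assumed to leave the AHI unchanged. The result is 9 per intervention, 18 in all, raised to 26 for 30% dropout.

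Section 2.6 gives every participant both interventions after a baseline evaluation.

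Section 2.8 compares baseline with A and B. For normally distributed data it specifies "Repeated-measures ANOVA with the Bonferroni correction for multiple testing, followed by Tukey’s honestly significant difference tests". Otherwise it specifies "the Kruskal–Wallis test with the Bonferroni correction for multiple testing followed by Dunn–Bonferroni tests". Neither sentence says which comparisons or outcomes the first-named Bonferroni correction covers.

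**The concern.** Tukey's HSD refers every pairwise difference to the studentized range for three conditions and uses one error term for all of them. In a repeated-measures setting this is accurate only if the three pairwise differences have equal variance. The article's own SDs, 8.6/h untreated and 5.8/h treated, suggest that they do not. Baseline variability then enters the standard error of A versus B, although baseline is not part of that contrast. A versus B is judged too strictly, and at least one comparison with baseline too leniently.

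Tukey already controls the error rate over the three pairs. If the Bonferroni correction covers those same pairs, the multiplicity is charged twice. If it covers something else, such as the ANOVAs across outcomes, the article does not say so, and the choice stays open until the data are seen.

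What is at stake is a real advantage of protrusion over the resting position being reported as no difference, and a threshold for the key contrast that is not fixed in advance.

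**Working it through.** **Inputs.** From 2.5: means 21.8 and 9.3/h, SDs 8.6 and 5.8/h, difference 12.5/h, α 0.05, power 0.80, 18 evaluable. From 2.6: each completer supplies both A and B, so 18 pairs. From 2.8: three conditions. Assumptions, because the article gives no values: B SD between 5.8 and 8.6, a common within-person correlation of 0 to 0.7, and normal data.

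**1. The plan's own sample size.** With σ = 8.6, d = 12.5/8.6 = 1.453. The exact two-sample t-test, two-sided 0.05, gives 9 per group (power 82.5%; 8 per group gives 77.1%). Then 18/0.7 = 25.7, rounded up to 26. The figure is reproduced, using an unadjusted test of A versus B. (2.5 writes a one-sided rule, which would give 7 per group at this SD; that is a separate matter.)

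**2. Thresholds with 18 completers.** Error df = 2 × 17 = 34. Unadjusted |t| = 2.03. Tukey, q(0.95; 3, 34)/√2 = 2.45, a per-comparison p of 0.020. Tukey at 0.05/3 = 2.92, a per-comparison p of 0.006.

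**3. Effect of the pooled error (correlation 0).** Expected MSE = (8.6² + 5.8² + s_B²)/3. Tukey takes 2 × MSE as the variance of every pairwise difference. The true variance for A − B is 5.8² + s_B². Dividing the threshold by the ratio of true to assumed SD gives the threshold actually applied.

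- B SD 5.8: MSE = 141.24/3 = 47.08 and 2 × MSE = 94.16, against a true 67.28. Ratio √(67.28/94.16) = 0.845. Effective |t| = 2.45/0.845 = 2.90, tail about 0.65%; with ÷3, 2.92/0.845 = 3.45, about 0.15%.
- B SD 8.6: MSE = 181.56/3 = 60.52 and 2 × MSE = 121.04, against a true 107.60. Ratio 0.943. Effective |t| = 2.60, about 1.4%; with ÷3, 3.09, about 0.4%.
- Baseline contrasts, Tukey alone. At B SD 5.8, baseline − A has true variance 73.96 + 33.64 = 107.60, ratio √(107.60/94.16) = 1.069, effective |t| 2.29, about 2.8%. At B SD 8.6, baseline − B has 147.92, ratio 1.105, effective |t| 2.22, about 3.3%. Tukey intends 2.0% per comparison. In this last case baseline − A has the same variance as A − B and is also judged strictly, so the leniency does not fall on every baseline contrast.

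Simulation over correlations 0 to 0.7 agrees. Under A = B the paired test rejects about 5%. Tukey rejects 0.4–0.7% at B SD 5.8 and about 1.5% at B SD 8.6 (individual runs 1.3–1.7%). With both corrections the rates are 0.1–0.2% and 0.3–0.5%.

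**4. Power at the planned difference (12.5/h, 18 pairs, correlation 0).** With all SDs 8.6, the noncentrality is 1.453 × √(18/2) = 4.36. Power is 96.8% against 2.45 and 91.6% against 2.92. With SDs 8.6/5.8/8.6, simulation gives 99.2% and 97.2%. At correlation 0.3 or more, power is about 98.4% or higher even with both corrections.

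**5. Power if B also works.** Illustration: B achieves half of A's effect, a difference of 12.5/2 = 6.25/h, with an assumed B SD of 7.2.

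| Correlation | Paired, 0.05 | Holm, three paired tests | Tukey | Tukey at 0.05/3 |
|---|---|---|---|---|
| 0 | 77% | 72% | 56% | 37% |
| 0.3 | 90% | 88% | 74% | 56% |
| 0.5 | 97% | 96% | 89% | 76% |
| 0.7 | 99.7% | 99.8% | 99% | 95% |

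Values are simulated; Holm was a separate run, so the last digit can differ. Check at correlation 0: noncentrality 6.25/√((33.64 + 51.84)/18) = 2.87 on 17 df gives 77% at 0.05 and 59% at 0.05/3. Holm must lie between these two.

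**The case against.** A reader might infer that power falls well below the stated 80%. The documents do not support that. The 80% belongs to 9 separate participants per intervention at 12.5/h. If A and B really were 9 separate patients each, power would be 69–72% with Tukey and 50–54% with both corrections. But 2.6 gives both interventions to everyone, so 18 pairs contribute, and step 4 shows power above 80% at the planned difference. A large loss appears only for a smaller A–B difference, and its size depends on B's effect and the correlation, neither of which the article gives.

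A reader might also infer that the correction is certainly applied twice. The text attaches Bonferroni to the ANOVA and names Tukey as the follow-up. It could be meant for the ANOVAs across the many outcomes, and Dunn–Bonferroni is a single named procedure. So double correction is plausible but not certain. What remains is that the family is unnamed, and that Tukey alone still brings the pooled error.

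Third, controlling error over three pairs is legitimate: the abstract and introduction hypothesise A against no control, B against no control, and A over B. This stands. Testing A versus B alone and first would be a preference, not a correction. Part of the gap between 77% and 56% is therefore a fair price for multiplicity; the Holm column shows how small that price can be.

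Finally, the error on A versus B is in the conservative direction and creates no false claim for A over B. This is true, but it does not hold for every comparison with baseline.

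**Conclusion.** The point holds as a mismatch between the sized contrast and the specified test, not as a power shortfall. Under A = B, a contrast sized at 5% would be rejected about 0.4 to 1.5% of the time with Tukey, and 0.1 to 0.5% if Bonferroni ÷3 is stacked on it. Some comparisons with baseline run at up to about 3% against Tukey's 2%. Part of the strictness is the ordinary three-pair adjustment; the rest comes from pooling unequal variances and from any second correction.

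The consequence is material if B improves breathing too, which the abstract, introduction and conclusions all expect although 2.5 assumes that B has no effect. At half of A's effect the loss is large at low correlation and small at 0.7.

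These figures rest on 18 completers, normality, the assumed B SD and correlation, and overnight AHI SDs standing in for ABI-A over one-minute periods. They show how the procedure behaves; they do not forecast the trial's results.

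**What to change.** In 2.8, replace Tukey's HSD and the added Bonferroni correction with three within-participant paired contrasts: A versus B, A versus baseline and B versus baseline. Test each on the participants' own differences with its own standard error, under one multiplicity procedure, for example Holm over these three pairs at two-sided 0.05. In the non-parametric branch, likewise apply one correction only and name its family. If an adjustment across outcomes is also intended, say so separately and list the outcomes.

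The cost is a change of wording before analysis, with no new participants or data. A versus B still carries some multiplicity adjustment under Holm, and 2.5 should say so, since it sizes that contrast unadjusted.

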## 2. Materials and Methods

### 2.1. Study Design

This is a randomized, controlled, non-blinded, crossover, and two-armed (i.e., sequence AB/BA) clinical trial that will follow the CONSORT 2010 statement, providing an extension to randomized crossover trials to better report the results [9]. An overview of the study is presented in Figure 2, following the recommended template for the schedule of enrollment, interventions, and assessments described by Standard Protocol Items: Recommendation for Interventional Trials (SPIRIT) [10]. Recruitment will last from the day the data are released by the Japan Registry of Clinical Trials (jRCTs) (032220040) (25 April 2022), and the duration of the study itself will start from the day the data are released by jRCTs until 31 March 2026.

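### The non-normal branch of section 2.8 applies independent-groups rank tests to repeated measurements on the same participants

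*Protocol article*

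**What the plan says.** Section 2.1 describes a "randomized, controlled, non-blinded, crossover, and two-armed (i.e., sequence AB/BA) clinical trial". Section 2.6 gives every participant a 1-minute baseline with the device in place, after which "each patient will undergo both interventions A (MAX50 for 1 min and MAX 100 for 1 min) and B (1 min) in a randomized order". All three conditions are therefore recorded on the same people.

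Section 2.8 sets the comparison: "The baseline measures will be compared with the measures obtained under interventions A and B". A Shapiro–Wilk test selects the method. For normal data the method is "Repeated-measures ANOVA with the Bonferroni correction for multiple testing", followed by Tukey tests. Otherwise "a non-parametric test, the Kruskal–Wallis test with the Bonferroni correction for multiple testing followed by Dunn–Bonferroni tests, will be used". The article names no related-samples rank test anywhere.

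**The concern.** Kruskal–Wallis and Dunn tests compare separate groups of people. Their reference distributions take every observation as independent of every other. Here each participant contributes one value to each group, so that assumption fails by design. The parametric branch treats the same data as repeated measures, so the error structure would change with the outcome of a normality test.

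This is a test that the article names, not a detail left to an analysis plan. It matters because the non-normal branch is the likely route for the primary outcome, ABI-A. At stake are the level of the primary p-value and the within-participant precision for which a crossover is normally chosen.

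**Working it through.** **Which N.** Section 2.5 states 9 per intervention, 18 in all, and 26 after 30% dropout. A two-sided two-sample t-test with difference 21.8 − 9.3 = 12.5 and SD 8.6 (d = 12.5/8.6 = 1.453) gives power 0.825 at 9 per group and 0.771 at 8, which reproduces 9. Then 18/0.7 = 25.7, so 26. The checks below use N = 18 and 26 participants, each measured under three conditions.

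**Which branch.** An apnea lasts more than 10 s (section 2.7.1), so at most five fit wholly into one minute. One event in a 1-minute window counts as 60/h, so ABI-A moves in steps of 60/h (30/h if the two minutes of A are pooled). In simulated gamma-Poisson 1-minute counts at 21.8/h (SD 8.6/h), Shapiro–Wilk rejected in 100% of samples at both N. It rejected in at least 99% at an assumed 60/h and in 57–100% at an assumed 120/h.

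**Effect on the level.** If the conditions share correlation ρ, the variance of a difference between two condition means is 2σ²(1−ρ)/n. The independent-groups test uses 2σ²/n. In large samples the Kruskal–Wallis statistic under the null then behaves roughly like (1−ρ) times a chi-square on 2 df (ρ taken on the ranks). The rejection rate is about 0.05^(1/(1−ρ)):
- ρ = 0.05: 0.05^1.053 = 4.3%
- ρ = 0.3: 0.05^1.429 = 1.4%
- ρ = 0.5: 0.05^2 = 0.25%

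Simulation agrees in direction and order of size (lognormal data, N = 18, 20,000 runs). Kruskal–Wallis rejects 4.9%, 1.6%, 0.5% and about 0% at ρ = 0, 0.3, 0.5 and 0.7. Friedman stays between 4.3% and 4.8%.

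**Effect on power, lognormal data, ρ assumed.** Steps of 0.3 SD between conditions, overall test:

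| ρ | N | Kruskal–Wallis | Friedman |
|---|---|---|---|
| 0 | 18 | 30% | 22% |
| 0.5 | 18 | about 21% | about 43% |
| 0.5 | 26 | about 36% | about 60% |
| 0.7 | 18 | about 16% | about 66% |

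For A vs B alone (N = 18, steps of 0.4 SD), Dunn–Bonferroni has power 9%, 6%, 4% and 2% at ρ = 0, 0.3, 0.5 and 0.7. The Bonferroni-adjusted signed-rank test has 7%, 11%, 15% and 26%.

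**What correlation the planning figures imply.** Read 8.6/h as between-person SD and take Poisson counts in one minute. The mean is 21.8/60 = 0.363. The between-person variance is (8.6/60)² = 0.0205 and the Poisson variance is 0.363. So ρ = 0.0205/(0.363 + 0.0205) ≈ 0.05.

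**Effect on power, 1-minute counts, N = 18** (rates falling from 1 to about 0.7 to about 0.43 of baseline):
- Planning rate and SD (ρ ≈ 0.05): null rejection about 4.0% vs 4.5–4.7%; power 12–13% vs 13–14%.
- 120/h with the same relative spread (ρ ≈ 0.24): Kruskal–Wallis null rejection 1.9%; power 56% vs 59%; unadjusted A vs B, rank-sum 24% vs signed-rank 29%.
- Mean 1 per minute, between-patient CV 1 (ρ = 1/(1+1) = 0.5 at equal rates): null rejection 0.3–1.0% vs 3.7–5.2% over separate runs; power 14–15% vs 31–32%.

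In each pair Kruskal–Wallis comes first and Friedman second, except where other tests are named.

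**The case against.** The strongest reply is that the argument for reaching this branch and the argument for harm can pull apart. Shapiro–Wilk fails because the outcome is a sparse count. At the planning rate and SD, that same sparse count implies a correlation of about 0.05, where the two tests differ by a point or two. The large losses need a correlation of 0.5 or more, which the article does not state. At zero correlation with continuous data Kruskal–Wallis is correctly sized and more powerful than Friedman. This stands, and it rules out any unconditional claim about lost power.

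It does not rescue the test. The planning figures are an AHI from a tongue-stabilizing-device study, whereas ABI-A is scored under sedation. Wider differences between patients would raise the correlation, and the mean 1 per minute, CV 1 case shows the effect. A plan that chooses a crossover also cannot sensibly rely on the pairing being absent.

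A reader might infer that a significant result from this branch would be spurious. The design does not support that: under positive correlation the p-values are too large, so a positive finding would not be an artefact of this choice. A reader might also infer that the normality gate must go and a single primary test must be named. Those are separate questions; replacing the test names is enough to cure this defect.

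**Conclusion.** Wrong as written. Section 2.8 names independent-groups tests for data that sections 2.1 and 2.6 make within-participant, it contradicts its own parametric branch, and nothing elsewhere in the article corrects it. The branch will very likely decide the primary outcome.

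The p-values lose their nominal level whenever measurements within a participant are correlated. If the correlation is positive, the exposure is to a missed effect. The loss ranges from negligible (correlation about 0.05) to moderate or severe (0.5 and above). The correlations, effect steps and count rates other than the planning rate are assumptions, so the power figures are scenarios and not forecasts. The counts were simulated as Poisson, which ignores the minimum event duration, and with one minute per condition, although section 2.6 records A at two positions for a minute each.

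**What to change.** In section 2.8, replace Kruskal–Wallis and Dunn–Bonferroni with related-samples methods: a Friedman test across baseline, A and B, followed by Bonferroni-adjusted Wilcoxon signed-rank comparisons. For A vs B, preferably use a rank-sum test between the two sequences on the within-participant period differences. That test also allows for a period effect, which the signed-rank test does not.

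The cost is one sentence of analysis text. No new data, participants or software are needed. The change should be made and dated before the outcome data are examined, so that the substitution is not made after the results are known.
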